### Measurements

Baseline and follow-up questionnaires for both the RCT and cohort study will be digitally administered using Castor EDC (https://www.castoredc.com). Questionnaires can be accessed through a link that will be sent via e-mail. Participants who have expressed a preference for hardcopy versions of the questionnaires will receive them at their home address. Participants will receive one reminder for each questionnaire, 2 weeks after the questionnaire has been sent. If participants do not return the six-month follow-up questionnaire, and unless they have withdrawn their participation from the study, they will receive the 12-month follow-up questionnaire. Table 1 provides an overview of all measurements incorporated in the questionnaires (primary and secondary outcomes and additional measurements; for cancer survivors and partners). Table 2 shows how all constructs will be operationalized, measured, and processed for further analyses, including references to individual questionnaires.

**Table 1 Tab1:** Overview of variables that will be measured in the STEPS randomized controlled trial (RCT) among cancer survivors and the cohort study among partners of cancer survivors

Category	Variable	RCT among cancer survivors				Cohort study among partners of cancer survivors			
		T0 (Baseline)	T1 (6-month)	T2 (12-month)	Variable^a^	T0 (Baseline)	T1 (6-month)	T2 (12-month)	Variable^a^
Work outcomes	Working hours per week	X	X	X	P	X	X	X	P
	Change in working hours (%)	X	X	X	S	X	X	X	S
	Employment status	X	X	X	S	X	X	X	S
	Time to return to work	X	X	X	S^b^				–
	Sick leave	X	X	X	S	X	X	X	S
	Readiness for return to work	X	X	X	S				–
	Work ability	X	X	X	S				A
Health outcomes	Health-related work functioning	X	X	X	S^c^	X	X	X	S
	Health-related quality of life	X	X	X	S	X	X	X	P
	Caregiver burden				–	X	X	X	S
	Depression	X			A	X	X	X	S
Sociodemographic	Age, gender	X			A, M	X	X		A
	Marital status	X			A	X	X		A
	Children living at home	X			A	X	X		A
	Education and income	X			A	X	X		A
	Breadwinner status	X			A	X	X		A
Medical	Cancer site	X			A, M	X	X		A^d^
	Time of diagnosis	X			A, M	X	X		A^d^
	Received and future treatment(s)	X			A, M	X	X		A^d^
	Cancer recurrence(s)	X			A	X	X		A^d^
Lifestyle	Smoking	X			A	X	X		A
	Alcohol consumption	X			A	X	X		A
	Physical activity	X			A	X	X		A
Health	Comorbidities	X			A	X	X		A
	Fatigue	X			A	X	X		A
Employment	Main tasks	X			A	X	X		A
	Years in current position	X			A	X	X		A
	Years of paid employment (and in current job)	X			A	X	X		A

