	Depression	The Centre for Epidemiological Studies Depression Scale [33];, consisting of 20 items and a range of 0 to 60, a score of 16 and over indicates the possible presence of clinical depression	20	0 to 60	Dichotomous
Sociodemographic	Age	Asking participants about their age (in years)	1	n/a	Continuous
	Gender	Asking participants about their gender (male/female)	1	n/a	Dichotomous
	Marital status	Asking participants about their marital status with answer options: Not married, married without children, married with children, living together with partner, living together with partner and children, living together with others, single with children, divorced, widow/widower.	1	n/a	Categorical
	Children	Number of children (living at home)	2	n/a	Continuous
	Education	Asking participants about their highest education level completed with eight outcome options according to the Dutch education system.	1	n/a	Categorized in low, middle, high (according to International Standard Classification of Education (ISCED-97).
	Income	Asking participants about their annual income (before tax) with answer options: <€30.000, €30.000–€60.000, €60.000–€100.000, and > €100.000.	1	n/a	Categorical
	Breadwinner status	Asking participants about their breadwinner status with answer options: being sole breadwinner, not being breadwinner, being shared breadwinner with partner, don’t know	1	n/a	Categorical
	Financial necessity of work	Asking about financial necessity of work	1	n/	Dichotomous
Medical	Cancer site*	Asking participants about their cancer site with 17 answer options (being the most common cancer sites) and the answer option ‘other’	1	n/a	Categorical
	Time of diagnosis*	Asking participants for their time of diagnosis, which can be calculated in the time since diagnosis.	1	n/a	Continuous
	Treatment(s)*	Received and future treatment(s). E.g. surgery, radiation, chemotherapy, hormonal therapy, or combination, and medication	1	n/a	Categorical
	Cancer recurrence(s)*	Asking about recurrence of cancer in the follow-up questionnaires.	1	n/a	Dichotomous
Lifestyle	Smoking	Asking participants about their smoking status with answer options: smoker, ex-smoker, non-smoker.	1	n/a	Categorical
	Alcohol consumption	Asking participants about their alcohol consumption with answer options: Never, only at festive occasions, several times a month, once a week, several times a week, daily.	1	n/a	Categorical

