	Caregiving leave	Asking participants whether they take caregiver leave (yes/no), and if so, for how many hours per week.	2	n/a	Dichotomous and continuous
Work	Social support from supervisor/colleagues	Two subscales of the validated Dutch version of the Job Content Questionnaire (JCQ [38];), with four items each (range 4–16).	8	4 to 16 (per subscale)	Continuous
	Job insecurity	One item (four point scale) of the Dutch Questionnaire on Perception and Judgment of Work (VBBA [39];).	1	4-point scale	Continuous
	Need for recovery	11-items (two point scale) of the VBBA [39].	11	0 to 22	Continuous
	Work accommodation	Structural changes in the job/function, and the contracted working hours, but also regarding offered and accepted accommodations, e.g., lighter work, reduced hours, modified tasks, more breaks, flexible schedule.	9	n/a	Categorical
	Impact of COVID-19 on work	Five self-established questions asking participants about the impact of COVID on their work.	5	n/a	Categorical
	Work attitude	Dutch version of the Work Involvement Scale [40]. The scale consists of six statements regarding work and working in general, that are all scored on a 7-point scale. A sample item is: ‘Having a job is very important to me.’	6	0–36	Continuous
	Self-efficacy	The Dutch version of the 12-item General Self-Efficacy scale [41] (range 12–60). A sample item is: ‘When I have decided to do something, I will definitely do it.’ The Dutch version consists of 10 items.	10	11–60	Continuous
	Work-family balance	Five questions (four point scale) from the Copenhagen Psychosocial Questionnaire (COPSOQ II [42];). A higher score indicates more work-family imbalance.	5	4-point scale	Continuous
	Work intention	One question: ‘In your estimation, what are the chances that you will be at work in 6 months?’, measured with a 10-point rating scale from 1 (no chance) to 10 (very high chance).	1	10-point scale	Continuous
	Fear of COVID-19	A Dutch translation (provided by our research group) of the fear of coronavirus-19 scale [43]. The scale consists of 7 items and is scored on a 5-point rating scale, ranging from 1 (strongly disagree) to 5 (strongly agree). A higher score indicates higher fear of COVID-19.	7	7–35	Continuous
	Expectations regarding return to work	Two questions indexing whether they have a return date in mind (yes/no), and if so, what that date is.	2	n/a	Dichotomous / continuous

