#### Cohort study among partners of cancer survivors

The primary outcomes for partners are working hours per week and health-related quality of life. Secondary outcomes include change in working hours (as a percentage of the contract hours at baseline), ‘employment status’ (at work/not at work), sick leave, health-related work functioning, caregiver burden and depression. Information on a number of additional parameters (see Table 1 for a full overview) will be gathered to describe the study sample and/or as predictors in the prediction model.

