#### Cohort study among partners of cancer survivors

Reason of non-response before baseline (from the answer card) and during the follow-up period will be tabulated to get a better understanding of the representativeness of our sample. The distribution of baseline values of primary and secondary outcomes and additional variables will be described. The longitudinal nature of the data enables examination of the course of primary and secondary outcome measures over time in partners, using GEE for longitudinal data with time as independent variable and the outcome variables as dependent variables.

A time lag prediction model will be used to determine which characteristics predict the primary outcomes in partners of cancer survivors [48]. In this time lag model, the measurements of the predictors will be related to outcomes status 6 months later, thus relating baseline (T0) predictors to outcomes at T1, and predictors at T1 to outcomes at T2 [51]. Univariate analyses with *p* < 0.10 will be conducted, to select possible relevant predictors. Continued selection on the remaining predictors from the univariate analyses will be based on multi-collinearity and accepted in the multivariate GEE analyses if correlation coefficients are ≥ − 0.7 and ≤ 0.7 [52].

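### Table 2 reduces partner depression, a 0–60 score and a secondary cohort outcome, to below 16 versus 16 or more, so the analysis of its course registers only crossings of the cut and loses precision

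*Protocol article*

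**What the plan says.** The text introducing the tables (Methods, Measurements) presents Table 2 as showing how each construct is measured and processed for analysis, so its last column is a stated analysis choice. The depression row describes a scale "consisting of 20 items and a range of 0 to 60", adds that "a score of 16 and over indicates the possible presence of clinical depression", and closes with "0 to 60 Dichotomous". No other form of the score is mentioned anywhere in the article.

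The partner cohort's secondary outcomes include "health-related work functioning, caregiver burden and depression". Table 1 schedules depression for partners at T0, T1 and T2 as a secondary outcome, and for cancer survivors at T0 only, as an additional variable. The cohort paragraph under Statistical analyses provides for "examination of the course of primary and secondary outcome measures over time in partners, using GEE for longitudinal data", with time as the independent variable. The time-lag prediction model in the same section is aimed at the primary outcomes only.

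**The concern.** The other multi-item outcome scales for partners (SF-12, work role functioning, caregiver burden) are all kept continuous in Table 2. Where two forms are meant, the table says so: caregiving leave is listed as "Dichotomous and continuous". The single entry for depression therefore does not read as shorthand for both forms, and the article gives no reason for treating this scale differently.

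With the binary form, a partner who moves from 15 to 17 counts as changed, while one who moves from 17 to 50, or from 2 to 15, counts as unchanged. The Background cites depression among partners as part of the motivation for the cohort, and the Discussion expects a substantial negative effect on partners' health. A general shift in depressive symptoms on either side of the cut could be estimated imprecisely or missed, although the score that would show it has been collected.

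**Working it through.** **1. The plan's own cohort size.** From Sample size calculation (cohort): 10 variables × 10 observations = 100 in the smallest outcome group. With the expected 50:50 split, 100 / 0.5 = 200. With 25% attrition, 200 / 0.75 = 266.7, so 267. Both stated figures reproduce. Depression is not named in this calculation, and the article states no figure for information loss.

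**2. Inputs for the loss.** From the documents: score range 0–60, cut at 16, about 200 partners analysed. Not in the documents, hence assumed:
- the share p at or above 16: 20–50%. The only split given is the 50:50 for partner outcomes in general;
- the shape of the score: roughly normal, with a skewed check in step 5;
- the correlation ρ between waves: 0.3–0.7.

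**3. Single-wave comparison.** A shift of δ standard deviations in a normal score moves the proportion above the cut by about φ(z_p)·δ, where z_p is the normal quantile leaving p above it. The efficiency of the split relative to the score is

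E = φ(z_p)² / [p(1 − p)].

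| p at or above 16 | E | Loss | 200 × E |
|---|---|---|---|
| 0.50 | 0.637 | 36% | 127 |
| 0.40 | 0.622 | 38% | 124 |
| 0.30 | 0.576 | 42% | 115 |
| 0.20 | 0.490 | 51% | 98 |

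Below the assumed range the loss grows: 57% at p = 0.15 and 66% at p = 0.10.

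**4. Within-person change, which is closer to the planned GEE on time.** The variance of a change between two waves is proportional to 1 − ρ for the score and to p(1 − p)(1 − ρ_b) for the indicator. Here ρ_b is the correlation between the two binary indicators, obtained from the bivariate normal distribution. So

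E_change = E × (1 − ρ) / (1 − ρ_b).

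| p | ρ | ρ_b | E_change | Loss |
|---|---|---|---|---|
| 0.50 | 0.3 | 0.194 | 0.553 | 45% |
| 0.50 | 0.7 | 0.494 | 0.377 | 62% |
| 0.20 | 0.3 | 0.163 | 0.410 | 59% |
| 0.20 | 0.7 | 0.456 | 0.270 | 73% |

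For example, at p = 0.50 and ρ = 0.3: 0.637 × 0.7 / 0.806 = 0.553. Splitting the score weakens the correlation between waves (ρ_b is below ρ), so within-person change gains less from the repeated measurement.

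**5. Skewed scores.** With gamma-distributed scores (means 8 to 16, SDs 7 to 10, giving 12–42% at or above 16), the single-wave loss is about 36–41% if all scores shift proportionally and 39–85% if all shift by the same amount. Skewness therefore does not remove the loss, but its size depends on the kind of shift.

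**The case against.** The strongest reply is that this is a choice of quantity, not a mistake. The share of partners with possible clinical depression is easy to interpret, the cut is fixed before the data are seen, and binary outcomes belong to the cohort's framework: the Abstract foresees logistic or linear regression, and the sample size speaks of positive and negative outcomes. Depression is one of six secondary outcomes in an observational cohort. It is not named in the sample-size calculation and is not a target of the prediction model. Health-related quality of life and caregiver burden, both continuous at all three waves, would pick up some of the same change.

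Most of this stands. It shows that the proportion at 16 or more deserves a place in the report, and that the stakes are low. It does not show why the proportion should be the only analysed form when the score exists.

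Three stronger readings are tempting, and the documents support none of them:
- **That a third to a half of the information is lost, as a fact.** That range holds for a single-wave comparison of a normal score at an assumed 20–50% prevalence. The planned analysis concerns change over three waves, and the documents give none of the quantities needed to fix its loss.
- **That the RCT has the same problem.** For survivors, depression is a baseline-only additional variable. Such variables may serve to describe the sample, and no RCT model is stated to use depression specifically.
- **That the cut-off itself is wrong.** Nothing in the documents contradicts it, and it is a legitimate secondary summary.

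**Conclusion.** The point holds as a low-priority improvement confined to the partner cohort. Table 2 fixes a binary form for an outcome collected as a 0–60 score, and the GEE of its course will be less precise for it. Under the assumptions set out above, the loss is about 36–51% for a single wave and about 45–73% for change between two waves. The second range is nearer to the planned analysis, but it rests on an assumed correlation and simplifies three waves to two. The direction is secure; the exact size is not. No primary result, sample size or RCT conclusion is affected.

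**What to change.** In the depression row of Table 2, set the partner operationalisation to *Continuous (0–60)* as the main form for the GEE, and name the proportion scoring 16 or more at each wave as a pre-specified supplementary clinical summary. Leave the survivors' baseline variable as it is.

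The score has to be computed before the cut can be applied, so the change needs no new data, participant burden or extra recruitment. The cost is a wording change made before analysis. If it counts as a substantial modification, it would also have to be registered and disclosed to the ethics committee, as the Design and setting section requires.

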#### RCT among cancer survivors

The primary outcome (i.e., working hours per week) will be assessed by asking cancer survivors about their current number of actual working hours. Hence, the primary outcome ranges from zero hours (for those on full sick leave) up to the number of working hours per week in the participant’s employment contract (for those fully returned to their work). This outcome was chosen as, according to the Dutch system, RTW is typically characterised by a gradual increase in work hours, while this measure is also important for workers trying to retain work. Secondary outcomes measures include: change in working hours (as a percentage of the contract hours at baseline), employment status (at work/not at work), sickness absence days, RRTW, work ability, health-related work functioning (only for cancer survivors who returned to work), time to RTW (only for cancer survivors who were on sick leave at baseline), and health-related quality of life. In addition to abovementioned outcome measures, information on a number of additional parameters (see Table 1 for a full overview) will be gathered, to describe the study sample, to include as potential confounder(s), and/or to conduct subgroup analyses.

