### Participants and recruitment

#### RCT among cancer survivors

Cancer survivors of working age (18–63 years at time of diagnosis), with histologically confirmed cancer and a life expectancy of more than 1 year will be recruited. At study entry, eligible cancer survivors have a fixed or temporary employment contract, with at least 6 months left of their contract, and a history of paid work for at least 1 year prior to diagnosis (with ≥8 contracted working hours per week). Cancer survivors can both be at work or (partly) on sick leave when entering the study. Cancer survivors will be recruited 3–18 months post-diagnosis. The cut-off for the maximum time post-diagnosis was set at 18 months for cancer survivors to be able to complete the intervention (with a maximum duration of 6 months) before a potential work disability assessment. According to Dutch legislation, work disability assessments take place after two years of sick leave to determine whether someone is disabled for work or not and may receive work disability benefits or not. Regardless of the outcome of the work disability assessment, employers are allowed to terminate the employment contract after 2 years of sick leave. Moreover, cancer survivors will be eligible for participation in STEPS if they are, or have been, treated with at least radiotherapy and/or chemotherapy. Previous research has shown that cancer survivors who received complex treatments, i.e., chemotherapy, radiotherapy, or a combination thereof, indicated lower work ability than cancer survivors who were treated with surgery alone [22]. Cancer survivors with additional treatment modalities, besides radiotherapy and/or chemotherapy, will be eligible for participation as well.

Cancer survivors will be excluded if their treating physicians consider work unfeasible, if cancer survivors have serious cognitive or psychiatric problems, or other comorbidities that would preclude them from participating in the intervention program, and/or if cancer survivors lack basic proficiency in Dutch. Cancer survivors participating in concurrent studies or rehabilitation programs aimed at sustained employment, or cancer survivors who refuse the involvement of their employer in the STEPS intervention will also be excluded.

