See Fig. 2 for a logic model of the STEPS intervention elements, and Supplementary file 2 for an overview of the intervention components per behavioural change stage. The STEPS intervention has a maximum duration of 6 months, during which cancer survivors receive a minimum of three and a maximum of nine sessions, depending on their work-related support needs. STEPS is aimed at supporting cancer survivors’ work-related self-efficacy during their RTW or work retention process, and to encourage them to develop and maintain effective communication with their employer. During the STEPS intervention, the cancer survivors’ behavioural change stage will be monitored continuously and the intervention will be tailored to the specific stage the survivor is in. To do so, cancer survivors will be asked to complete a brief questionnaire (i.e., a Dutch version [25] of the Readiness for Return To Work - RRTW [15]) and an abbreviated version of the Return to Work Obstacles and Self-Efficacy Scale - ROSES [26]) prior to each session with the occupational therapist. Based on the outcomes of the RRTW questionnaire, participants will be categorised according to one of the six stages of change (pre-contemplation, contemplation, preparation: self-evaluative, preparation: behavioural, uncertain and proactive maintenance). Within each of these stages, participants will furthermore be given a traffic light designation (i.e. red, orange or green), based on the outcomes of the ROSES questionnaire, depicting potential barriers and facilitators regarding sustained employment and their overall progress within the intervention. Based on this categorisation the occupational therapist can, using the STEPS handbook, tailor the intervention provided (see Supplementary File 2).

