	Contract type (fixed/temporary)	X			A	X	X		A
	Shift work	X			A	X	X		A
	Company size and sector	X			A	X	X		A
	Time since first day of sick leave	X			A				–
	Employment status partner (if applicable)	X			A				–
	(duration of) Caregiving leave				–	X	X		A
Work	Social support from supervisor/colleagues	X			A	X	X		A
	Job insecurity	X			A	X	X		A
	Need for recovery	X			A^c^	X	X		A
	Work accommodation	X			A^c^	X	X		A
	Impact of COVID-19 on work	X			A^c^	X	X		A
	Work attitude	X			A	X	X		A
	Self-efficacy	X			A	X	X		A
	Work-family balance	X			A^c^	X	X		A
	Work intention	X			A	X	X		A
	Fear of COVID-19	X			A	X	X		A
	Expectations regarding return to work	X			A				–
Process measures			X		P				–
Economic evaluation	Quality of life	X	X	X	E				–
	Health care consumption	X	X	X	E				
	Productivity loss	X	X	X	E				

^a^*P* Primary outcome variable, *S* Secondary outcome variable, *A* Additional variable, *M* Modifier, *E* Economic evaluation variables, *P* Process variables

^b^Only completed by participants who were on sick leave at baseline

^c^Only completed by participants who (partly) returned to work

^d^The partner will be asked regarding the medical status of the cancer survivor

**Table 2 Tab2:** List of primary, secondary and additional variables and their assessment methods

		Instrument	# items	Rating scale	Operationalization
Work outcomes	Working hours per week	Asking participants for their current number of actual working hours	1	n/a	Continuous
	Change in working hours (%)	Asking participants for their current number of actual working hours and their contractual working hours at baseline.	1	n/a	Continuous (actual working hours at follow-up as a percentage of contractual working hours at baseline).
	Employment status	Asking participants whether they are at work or not at work	1	n/a	Dichotomous
	Time to return to work	Asking participants about their first day of returning to work, from which we will estimate the number of calendar days between the first day of sick leave and the first day of work, either fulltime or part-time, for at least 28 consecutive days without recurrence.	1	n/a	Continuous
	Sick leave	Asking participants about the number of days they have been on sick leave in the past 6 months	1	n/a	Continuous

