#### RCT among cancer survivors

Representativeness of participants will be evaluated by comparing cancer survivors who are included in the RCT with aggregated data of all potentially eligible cancer survivors from the NCR, using students’ t-test or appropriate non-parametric tests for the following characteristics: gender, age, time of diagnosis, tumour type and stadium and treatment. Moreover, reason of non-response at baseline (from the answer card) and during the follow-up period will be tabulated to get a better understanding of the representativeness of the study sample.

Baseline sociodemographic and clinical characteristics of the intervention group and the control group will be described and compared. Primarily, all analyses will be conducted on an intention-to-treat basis. In addition, per-protocol analyses will be carried out, in which only cancer survivors who fully complete the intervention according to protocol (i.e., having completed a minimum of three sessions: an introductory session, at least one one-on-one session with an occupational therapist, and at least one session with the reintegration consultant) will be compared to the control group.

To evaluate between-group differences on the aforementioned primary and secondary outcomes, generalized estimating equations (GEE) for longitudinal data (i.e., with the primary and secondary outcomes at six (T1) and 12 months of follow-up (T2)) will be used, adjusted for baseline values of the outcome and using appropriate tests for ordered and continuous data. This approach accounts for correlated within-subject responses, allows for non-normally distributed variables and deals adequately with missing data [46–48]. If the data are not missing completely at random, non-ignorable drop-out will be adjusted for [49]. Short- (T1) and long-term (T2) effects of the intervention will be reported separately. Effect sizes will be expressed in beta, with 95% confidence interval.

The secondary outcome ‘time to RTW’ will be analysed with time-to-event analysis [50]. A Kaplan-Meier curve will be drawn, and differences between the two groups will be tested with the log rank test. In addition, the Cox proportional hazard model of survival analysis will be applied to estimate hazard ratios and the corresponding 95% confidence intervals.

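### Work functioning is compared between arms only among people at work, a set STEPS is meant to change, and adjusting for its own baseline removes those who return from full leave

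*Protocol article*

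**What the plan says.** In the Measurements section for the trial among survivors, the secondary outcomes include "health-related work functioning (only for cancer survivors who returned to work"). Table 1 schedules this outcome at T0, T1 and T2 and marks it with footnote c: "Only completed by participants who (partly) returned to work". Entry is open to people in any work state: "Cancer survivors can both be at work or (partly) on sick leave when entering the study".

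The Statistical analyses section for the trial states: "Primarily, all analyses will be conducted on an intention-to-treat basis". Between-group differences on the primary and secondary outcomes are then assessed by one GEE approach with T1 and T2 as outcomes, "adjusted for baseline values of the outcome". Models with and without confounder adjustment are promised for all analyses, and drop-out is to be adjusted for if data are not missing completely at random. Nothing is said about an outcome that does not exist because the person is not working.

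The same section adds a per-protocol analysis in which "only cancer survivors who fully complete the intervention according to protocol", meaning at least three sessions, "will be compared to the control group". The STEPS intervention section says that "cancer survivors receive a minimum of three and a maximum of nine sessions, depending on their work-related support needs".

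**The concern.** WRFQ can be scored only in someone who is working. Whether someone is working at six or 12 months is decided after randomisation. It is a secondary outcome in its own right, is closely tied to the primary outcome, and is something the Discussion expects STEPS to improve. If STEPS brings or keeps more people with limitations at work, the STEPS workers are a less selected group than the control workers. Their mean WRFQ can then be lower although nobody's functioning was harmed, so the outcome could count against STEPS because STEPS worked.

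The baseline adjustment adds a second problem. A participant on full leave at T0 has no baseline WRFQ. With complete-case handling of covariates, that person contributes nothing even after returning to work. The model is then confined to people working at both T0 and follow-up and is silent about return to work, one of the programme's two aims.

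**Working it through.** **Planning figures.** With a difference of 5.5 h, SD 13 h, two-sided alpha 0.05 and power 80%: n per arm = 2 × (1.96 + 0.84)² × 13² / 5.5² ≈ 88, so 176 in total, as stated. Allowing for 25% attrition, 176 / 0.75 ≈ 235, against the stated 236. These figures are sound and not in dispute. The 88 per arm serves below only as the number analysable.

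**Can the WRFQ analysis be intention-to-treat?** The primary outcome can: the Measurements section counts full sick leave as zero hours, so everyone has a value. No value is assigned to WRFQ for people not at work. The drop-out clause does not fill the gap, because someone on full leave who returns every questionnaire has not dropped out.

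**Size without baseline adjustment.** Assumptions: true effect on functioning zero; 64% of controls at work (the Background's general return-to-work figure, borrowed as an illustration); a normal propensity to be at work, correlated ρ with functioning. The mean among workers, in SD units, is ρ × φ(c)/p, where p is the share at work and c = Φ⁻¹(1 − p).

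- Controls, p = 0.64: φ(c)/p = 0.374/0.64 = 0.585
- STEPS, p = 0.79 (+15 points): 0.288/0.79 = 0.365
- Difference with ρ = 0.5: 0.5 × (0.365 − 0.585) = −0.11 SD

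| Points added at work | Bias, ρ = 0.5 | False-positive rate (nominal 5%) |
|---|---|---|
| 0 | 0 | 5.0% |
| +5 | −0.04 SD | 5.5% |
| +10 | −0.07 SD | 7.1% |
| +15 | −0.11 SD | 10.0% |
| +20 | −0.15 SD | 14.4% |

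At +15 points, ρ from 0.3 to 0.7 gives −0.07 to −0.15 SD.

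**Size with the planned baseline adjustment, complete cases.** A simulation of 2,000,000 participants per scenario, with one follow-up visit and a true effect of zero, assumed 50% at work at T0, 64% of controls at work at follow-up, and a common health factor linking work status and functioning. The regression used only people working at both times and adjusted for baseline WRFQ.

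| Points added at work | Bias, adjusted | Share of randomised in model |
|---|---|---|
| 0 | 0.00 SD | 36% |
| +10 | −0.05 SD | 38% |
| +15 | −0.08 SD | 39% |
| +20 | −0.11 SD | 40% |

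Baseline adjustment reduces the bias without removing it, and uses about two fifths of those randomised. The remaining bias arises because the simulated STEPS effect on being at work also reaches people working at T0. If STEPS affected only return from full leave, this restricted contrast would be unbiased for baseline workers, but uninformative about returners.

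**Per-protocol contrast.** Selecting completers in one arm shifts that arm's mean by ρ × SD × φ(c)/q, where q is the completion share. With true effect zero, q = 0.80 and ρ = 0.3: 0.3 × 13 × 0.35 = +1.4 h, or 25% of the planned 5.5 h. The range runs from +0.25 h (q = 0.90, ρ = 0.1) to +4.2 h (q = 0.60, ρ = 0.5). A negative ρ reverses every sign. The protocol gives neither q nor ρ.

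**The case against.** WRFQ is one of eight secondary outcomes listed, and the primary comparison is untouched. Functioning at work is a sensible question only for people at work. Work ability and quality of life are planned without that restriction, so the trial is not blind to the health of people on leave. How a missing baseline covariate enters a GEE is often left to an analysis plan, and confounder-adjusted models may reduce the bias. All of this stands, and it limits the weight of the point. It does not answer it: the restriction to workers, the between-arm comparison and the baseline covariate are all fixed in the protocol text, and adjustment for measured covariates does not guarantee a repair.

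A reader might infer that neither the WRFQ nor the per-protocol comparison can estimate any effect of STEPS. That goes too far. The WRFQ bias is zero if STEPS does not alter who is at work, and the per-protocol bias is zero if completion is unrelated to prognosis.

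A reader might also picture a large spurious deficit from newly returned, lower-functioning STEPS workers pulling down that arm's mean. Such a calculation describes an unadjusted mean. In the planned baseline-adjusted model under complete-case handling, those returners are exactly the people left out.

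Lastly, a reader might expect the per-protocol result to flatter STEPS because completers are fitter. The documents do not support a direction. The number of sessions follows support needs, and people fully back at work are eligible, so those doing well may stop early. The analysis is also explicitly additional to intention-to-treat.

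**Conclusion.** The point holds for WRFQ, conditionally. If STEPS changes who is at work, as the protocol hypothesises, the between-arm comparison among workers is not protected by randomisation and cannot be intention-to-treat as announced. On assumed inputs the bias is modest: −0.05 to −0.11 SD in the baseline-adjusted complete-case analysis for +10 to +20 points at work, and zero for no change. These sizes rest on an assumed 50% at work at T0, 64% of controls at work at follow-up, and moderate correlations between work status and functioning. The loss of returners from full leave depends on complete-case handling, for which the protocol states no alternative. The per-protocol contrast deserves a label rather than an objection: it selects in one arm only, with a bias of unknown sign. This is worth correcting, but it does not threaten the primary result.

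**What to change.** Do not make baseline WRFQ a required covariate. Use baseline work status and baseline work ability, both collected at T0 from everyone, so that people returning from full leave stay in the analysis. Report WRFQ by arm among workers as a descriptive, non-randomised comparison, always beside the share at work in each arm, without a confirmatory between-arm test. State that this outcome is an exception to the intention-to-treat rule. The cost is a change of wording, and one secondary outcome loses its test; no new data are needed.

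A rank-based composite that places not being at work lowest could be a sensitivity analysis. It is optional because it changes the question from functioning at work to a mixture with employment status.

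For the per-protocol analysis, add a sentence saying that it is non-randomised and will not be read as the effect of STEPS. A complier average causal effect, with randomised arm as instrument, is an option, but it must state its assumption that fewer than three sessions have no effect. That is doubtful here, since the introductory session already sets goals and a plan. Table 3 also takes completion from the patient process questionnaire sent with T1, so completion status may be missing for people who do not respond at T1.
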